## Abstract

**Background:**

Tooth decay is a significant public health problem globally. The caries-arrest effectiveness of 38% silver diamine fluoride (SDF) has been well documented. However, information on the caries-preventive effect of SDF on primary teeth is insufficient.

**Objective:**

The aim of this trial is to investigate the effectiveness of semiannual application of 38% SDF and that of 5% sodium fluoride (NaF) varnish when compared with placebo control for preventing occlusal caries in the primary molars of preschool children over 30 months.

**Methods:**

This 3-arm, parallel design, double-blind, randomized controlled trial involves 791 preschool children. Children are randomly allocated to receive 1 of 3 interventions as follows: Group 1, 38% SDF; Group 2, 5% NaF varnish; and Group 3, placebo control (tonic water). The intervention and dental examination will be carried out every 6 months. A parent-administered questionnaire, including the children’s demographic background and oral health–related behaviors, has been collected at baseline. Follow-up examinations to detect new caries development will be conducted every 6 months by a masked examiner. Caries development will be diagnosed at the cavitation level. Chi-square tests and logistic regression analyses will be adopted. A 2-level logistic regression analysis will be performed to investigate the effects of the study interventions and other potential confounding factors on the development of occlusal caries.

**Results:**

This study was started on September 1, 2020, and the recruitment process ended on September 30, 2021. At present, a total of 791 children are participating in the study. This 30-month clinical trial is expected to be completed in March 2024.

**Conclusions:**

If SDF application is more effective than NaF varnish for preventing caries on occlusal surfaces of primary teeth, it can be a preferred choice for caries prevention in a kindergarten-based program. Results of this trial will provide valuable clinical evidence for the development of oral health strategies and policies on the promotion of child oral health.

**Trial Registration:**

HKU Clinical Registry HKUCTR-2844, https://tinyurl.com/bdhz9yuk; ClinicalTrials.gov NCT05084001, https://clinicaltrials.gov/ct2/show/NCT05084001

**International Registered Report Identifier (IRRID):**

DERR1-10.2196/35145

## Introduction

### Background

Tooth decay or dental caries is a silent epidemic. According to the Global Burden of Disease Study, dental caries in primary teeth remains a public health problem affecting more than 530 million children globally [1]. The term “early childhood caries” (ECC) has been used to describe the presence of one or more decayed, restored, or missing primary teeth in a child younger than 6 years [2]. In Hong Kong, more than half (55%) of 5-year-old children have untreated ECC, and the majority (>90%) of the decayed teeth are left untreated [3]. Children with untreated ECC may experience toothache, oral pain, and infection, leading to poor quality of life [4]. This also affects their family members’ quality of life and eventually impacts the community. Severe consequences of ECC include emergency room visits and hospitalizations with high costs of treatment, and missing school, as well as negative impacts on the ability to learn [2]. In extreme cases, untreated ECC can lead to life-threatening conditions and even death [5].

An epidemiological study found that most (78%) cases of ECC in preschool children in Mainland China involved the primary molars [6]. In Hong Kong, decayed primary molars constituted more than half (56%) of all decayed primary teeth in preschool children [7]. High prevalence of premature loss of primary molars due to untreated tooth decay has been reported [8]. Tooth decay is commonly found on the occlusal tooth surface owing to the complex anatomy of the fissure system, which makes the surface difficult to clean, thereby promoting the accumulation of a bacterial biofilm and increasing the risk of developing carious lesions [6]. In addition, young children are not able to brush their posterior teeth properly, and they may not have supervised toothbrushing during the preschool period. Hong Kong preschool children’s oral health has not improved over the last 2 decades [9]. An epidemiological dental survey in Hong Kong found that the prevalence of caries was much higher in older preschool children (38% at age 3 years and 55% at age 5 years) [3]. Currently, there is no government-subsidized dental care service for preschool children in Hong Kong.

Several strategies, including placement of dental sealant and topical application of sodium fluoride (NaF) varnish, have been proposed to prevent occlusal surface caries. Nevertheless, it is a challenge to place dental sealants in the primary molars of young children because the application is technique sensitive and requires optimum tooth isolation. NaF varnish is another potential agent for preventing dental caries, but it is not cost-effective in the context of government-funded services [10]. The relatively high cost of professionally administered fluoride varnish has hindered its widespread adoption in many countries [11]. Recently, silver diamine fluoride (SDF) has been considered a therapeutic agent for treating cavitated dental caries lesions in young children and those with special needs [12]. Several laboratory studies have documented its antibacterial effects in inhibiting cariogenic bacteria and its remineralizing effects [13]. Results of randomized clinical trials have shown its caries-arresting effects in preschool children [14-16]. No major adverse effects of SDF were observed, except dark staining on treated lesions after application [17]. A systematic review concluded that the caries arrest rate of 38% SDF was as high as 81% (95% CI 68%-89%; *P*<.001) [18]. In light of this, the American Academy of Pediatric Dentistry developed a guideline on the use of 38% SDF for arresting cavitated dentin caries lesions in primary teeth among children [12]. Recently, another systematic review and network meta-analysis concluded that semiannual application of 38% SDF solution showed the highest effectiveness for caries arrest in advanced cavitated lesions on coronal surfaces [19].

Nevertheless, clinical evidence for the dental caries–preventive effect of SDF is scarce [20]. Therefore, to fill this knowledge gap and to provide the needed clinical evidence to guide dental practice and public dental care service, this study aims to investigate the preventive effect of SDF versus NaF varnish and a placebo control on the occlusal surfaces of the primary molars of preschool children. In addition, this study will evaluate parental satisfaction with their child’s dental status and dental appearance, and the adverse effects of SDF application.

### Objectives

The objective of this study is to compare the effectiveness of 38% SDF, 5% NaF varnish, and a placebo control for preventing dentine caries in the primary molars of preschool children when applied semiannually over 30 months.

### Hypothesis

The null hypothesis tested is that there is no difference in the effectiveness of 38% SDF, 5% NaF varnish, and a placebo control for preventing dentine caries of the occlusal surfaces of the primary molars in preschool children when applied semiannually over 30 months.

## Methods

### Ethics Considerations

Ethics approval has been obtained from the Institutional Review Board of The University of Hong Kong/Hospital Authority Hong Kong West Cluster (HKU/HAHKWIRB; IRB reference number: UW20-028).

### Trial Design

This is a 3-arm, parallel-design, double-blind, randomized controlled trial consisting of semiannual application of SDF, semiannual application of NaF varnish, and a placebo control. Similar school-based oral health education will be provided to the children and parents in all participating kindergartens. This study will be reported following the SPIRIT (Standard Protocol Items: Recommendations for Interventional Trials) guidelines (Multimedia Appendix 1). Before subject recruitment, the study was registered on January 17, 2020, at HKU Clinical Registry, which is a publicly accessible database, with the reference number HKUCTR-2844. Later, it was registered as a clinical trial by the United States National Library of Medicine (ClinicalTrials.gov) on October 19, 2021, with the registration number NCT05084001, as an additional registration.

### Patient and Public Involvement

Kindergartens that have participated in the school oral health program provided by the Faculty of Dentistry, The University of Hong Kong were invited. Research assistants will assist in all stages of the trial, mainly as contact persons and as persons in charge of inviting kindergartens, explaining the whole trial to kindergartens, and clarifying their queries. After the principals agreed to take part in this study, an information sheet containing the aim of the study and the details of the research study and procedures was distributed to parents or guardians of the children. Parental consent in written form was obtained before conducting this trial. The participant children and their parents are at liberty to withdraw from this study at any time. They are also free to seek further dental treatment with their own means and preferences.

### Eligibility Criteria

The eligibility criteria for participants are as follows: (1) age 3-4 years, (2) healthy status, (3) presence of at least one caries-free (no cavitation) primary molar, and (4) parental written consent. The exclusion criteria are as follows: (1) no cooperation or refusal to undergo examination, (2) major systemic illnesses, (3) presence of acute pain, infections, gingival ulceration, or stomatitis, (4) known sensitivity to silver or other heavy-metal ions, and (5) current involvement in any other research that may impact this study. At the tooth level, primary molars with developmental defects; presence of dental sealants or fillings; presence of pain, fistulas, abscesses, mobility, or discoloration; or any sign of nonvitality are excluded.

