### Recruitment and Examination

All phases of this trial will be carried out in the kindergarten that the children attend. The research team includes dentists and research assistants. Before conducting the trial, the whole team was trained by experienced specialists in dental public health. A calibrated and trained examiner screened the children who had written parental consent. All children were clinically examined, and those who met the inclusion criteria were selected. No dental radiograph examination was conducted. If a child has more than one caries-free primary molar, all of the molars will be included. At baseline and the semiannual follow-up examinations, clinical examination of the children will be conducted by a trained dentist who will be masked to the group assignment of the participant children. All clinical investigations will be conducted in kindergartens. The study children will lie on a bench and will be examined in the supine position. Tooth status will be assessed by careful visual inspection with a dental mirror attached to a handle with a light-emitting diode for intraoral illumination (MirrorLite, Kudos Crown Limited). A microbrush will be used to remove food debris and dental plaque that obstruct inspection. A World Health Organization CPI probe with a 0.5-mm ball tip will be used to confirm the presence of a carious cavity when necessary. Great care will be taken to avoid damaging the tooth surface during probing. The intervention will be free, and participants or kindergartens will not pay any cost for the research. After the examination, parents will receive a brief report on their children’s dental caries status.

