Caries will be diagnosed at the cavitation level following the criteria recommended by the World Health Organization. Drying of the tooth surface with air blow will not be carried out in this study. An occlusal tooth surface will be recorded in one of the following categories: (1) sound, (2) caries confined to the enamel or into dentin but without cavitation, (3) cavitated dentin caries (active), (4) cavitated dentin caries (arrested), (5) filled surface, (6) extracted tooth, and (7) tooth with nonvital signs, such as abscess or fistula. The decayed, missing, and filled tooth surface (dmfs) index will be adopted for documenting dental caries experience. Oral hygiene status will be measured using the visible plaque index (VPI). The buccal and lingual surfaces of 6 index teeth (Fédération Dentaire Internationale tooth numbers 55, 51, 63, 71, 75, and 83) will be thoroughly examined. The presence or absence of visible plaque on the occlusal surface will be recorded. Black staining on each surface will be clinically observed and recorded (yes/no). A random sample of 10% of the study children will be re-examined on the same day at the baseline and follow-up examinations to evaluate intraexaminer reproducibility. The study follow-up is every 6 months. If some parents of the study children seek early professional intervention, all the sealed, restored, or extracted teeth will be recorded as study treatment failure.

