### Interventions

Occlusal molar surfaces without cavitated dentine caries lesions were randomly allocated to receive SDF, NaF varnish, or a placebo control. Clinical examinations will be conducted every 6 months after the intervention.

The treatment interventions are as follows: (1) Group A, semiannual topical application of 38% SDF solution (Saforide, Toyo Seiyaku Kasei Co, Ltd); (2) Group B, semiannual topical application of 5% NaF varnish (Duraphat, Colgate Palmolive); (3) Group C, semiannual topical application of a placebo control (tonic water).

The application procedure is as follows:

Remove food debris and dental plaque, if any, from the occlusal surface to allow good contact between the study agent and tooth surface.Isolate the occlusal surface of sound primary molars with cotton roll or gauze. For Group A, dispense 1 drop (0.05 mL) of 38% SDF solution, which contains approximately 2.2 mg fluoride ions, in a plastic dappen dish. For Group B, dispense 1 drop (0.25 mL) of 5% NaF varnish, which contains approximately 5.6 mg fluoride ions, in a plastic dappen dish. For Group C, dispense one drop (approximately 0.05 mL) of tonic water in a plastic dappen dish.Slightly bend a microapplicator, and dip it in the agent.Apply the agent with the microapplicator directly onto the occlusal surface of sound primary molars in each quadrant. One application is used for 1 quadrant (1 or 2 primary molars). If a child has 8 sound molars, he or she will receive a maximum of 4 applications on that day.Gently rub the occlusal surfaces with the microapplicator while continuing to isolate the treated teeth whenever possible and ensure that the entire occlusal surfaces are wetted by the agent.Minimize contact of the SDF solution with adjacent gingiva or mucosa to avoid potential soft-tissue irritation.

Subsequently, the study children will be instructed not to eat and drink for 30 minutes after application. The intervention will be provided every 6 months. Application of the appropriate agent (either 38% SDF, 5% NaF, or tonic water) will be carried out after an oral examination according to the assigned treatment group. The schedule of subject enrollment, interventions, and outcome assessments is shown in Figure 1.

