### Sample Size Calculation

Based on previous studies [3,21], the anticipated proportion of sound occlusal surfaces at baseline developing into cavitated dentin lesions at the 30-month follow-up is approximately 25%. An absolute difference of 10% in the rate of new caries development (proportion of occlusal surfaces that develop cavitated dentin lesions at 30 months) between 2 intervention groups is considered to be clinically significant. The estimated sample size is based on the expected proportion of the development of new cavitated occlusal caries in primary molars, with the power of the study set at 90% (β=.1) and with a 2-sided test at the 5% statistical significance level. The sample size per study group, calculated by using the G*Power 3.1.9.2 software (University of Düsseldorf, Germany) is 351 sound occlusal tooth surfaces. The estimated intraclass correlation coefficient (ICC) for dental caries data at the surface level within the individual is approximately 0.5 [22]. Based on our previous survey [3], we anticipated that the mean number of sound occlusal surfaces per child would be 6 at baseline. Following the equation for the required sample size in a multilevel model, the design effect will be 3.5. Thus, the estimated sample size would be at least 1229 sound occlusal surfaces and with at least 205 children in each study group or 615 in total at baseline. The anticipated dropout rate after 30 months is 20%. Thus, 769 children in total need to be recruited at baseline. The estimated participation rate is approximately 90%, and therefore, at least 854 children have to be invited to join the study.

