A chi-square test and *t* test will be performed, when appropriate, to assess the differences between groups with regard to their baseline demographic background, oral health–related behaviors, and caries experience. A chi-square test will be used to evaluate the differences in new caries development and parental satisfaction among groups. Thus, 2-level generalized estimating equation models with a logit link function (child level and surface level) will be adopted to evaluate the variables influencing the occurrence of occlusal caries at the 30-month follow-up. Independent variables include the child’s background characteristics (gender, place of birth, father’s and mother’s education levels, and family income); the child’s clinical characteristics at baseline (tooth type, such as upper or lower molars and first or second molars, presence of plaque on the occlusal surface, caries experience, and overall oral hygiene); and the child’s oral health–related behaviors (use of fluoride agents, dental visit behavior, and snacking habit). The backward elimination method will be adopted for modeling. A McNemar test will be performed to compare the differences in parent’s satisfaction with their child’s dental appearance and dental health at baseline and the 30-month follow-up. The level of statistical significance for all tests will be set at .05. An intention-to-treat (ITT) analysis will be adopted so that all study children who are randomized and all events will be accounted for in the primary analysis. The relevant government agencies have access to the collected data for the purposes of verifying the integrity of the study data and evaluating compliance with the study protocol. Regarding confidentiality, hard copies of the data will be stored in a sealed box in a locked room during the trial and after publication for 5 years. In addition, the research findings will be presented in scientific conferences for clinicians and health care researchers, and will be disseminated to the community and stakeholders through oral health educational seminars and talks.

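### Enrolment and allocation admit non-cavitated lesions while application and sample size refer to sound surfaces, and the recorded baseline code separating the two is not a named covariate

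*Protocol article*

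**What the plan says.** The protocol article describes the study surfaces in two ways.

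- **Enrolment.** Eligibility Criteria ask for "presence of at least one caries-free (no cavitation) primary molar". Recruitment and Examination adds: "If a child has more than one caries-free primary molar, all of the molars will be included". The tooth-level exclusions do not name non-cavitated lesions; the nearest wording is "presence of pain, fistulas, abscesses, mobility, or discoloration; or any sign of nonvitality are excluded".
- **Recorded codes.** Recruitment and Examination gives sound surfaces code 1 and a separate code 2 for "caries confined to the enamel or into dentin but without cavitation".
- **Allocation.** Interventions opens with "Occlusal molar surfaces without cavitated dentine caries lesions were randomly allocated".
- **Application.** The steps in the same section say: "Apply the agent with the microapplicator directly onto the occlusal surface of sound primary molars in each quadrant".
- **Sample size.** The 25% rate is "the anticipated proportion of sound occlusal surfaces at baseline developing into cavitated dentin lesions". The mean of 6 surfaces per child is also for sound surfaces.
- **Primary Outcome.** It refers to an occlusal surface at baseline without giving its status.
- **Model.** The baseline clinical covariates named in Data Analysis are tooth type and "presence of plaque on the occlusal surface, caries experience, and overall oral hygiene". Backward elimination is then applied.

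**The concern.** If *no cavitation* defines the study surfaces, codes 1 and 2 are both in. If *sound* defines them, only code 1 is. The article uses the first for enrolment and allocation and the second for application and sample size, so a reader cannot tell whether the enrolled, treated and analysed surfaces are one set.

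This matters for interpretation. The Objectives and Hypothesis concern preventing dentine caries, and the Discussion names primary prevention as the knowledge gap. Code 2 includes lesions already in dentin, where cavitation can still be prevented but dentine caries cannot. A benefit on codes 1 and 2 together could come from sound surfaces staying sound, from existing lesions progressing more slowly, or from both. The code that would separate these is collected at baseline but not named in the model, although surfaces with a lesion can be expected to cavitate more often.

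**Working it through.** **1. The wording, side by side**

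| Step | Section | Term used | Codes admitted |
|---|---|---|---|
| Enrolment | Eligibility Criteria; Recruitment and Examination | no cavitation | 1 and 2 |
| Allocation | Interventions, first sentence | no cavitated dentine lesion | 1 and 2 |
| Application | Interventions, steps | sound | 1 |
| Sample size inputs | Sample Size Calculation | sound | 1 |
| Outcome denominator | Primary Outcome | status not given | unclear |

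**2. Can a named covariate stand in for the code?** Caries experience is measured by dmfs, with caries diagnosed at cavitation level, so a code 2 surface adds nothing to it. Tooth type, plaque and oral hygiene do not record a lesion on the surface.

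**3. The protocol's own sample size.** Inputs from Sample Size Calculation: 25% vs 15%, two-sided 5%, power 90%, ICC 0.5, 6 surfaces per child, dropout 20%, participation 90%.

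- Fisher's exact test has power 0.8995 at n = 350 and 0.9004 at n = 351, so 351 per group is reproduced.
- Design effect = 1 + (6 − 1) × 0.5 = 3.5.
- 351 × 3.5 = 1228.5, stated as 1229 surfaces; 1228.5 / 6 = 204.75, stated as 205 children per group; 3 × 205 = 615.
- 615 / 0.8 = 768.75, stated as 769; 769 / 0.9 = 854.4, stated as 854.

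The calculation is internally correct, for sound surfaces.

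**4. Power on code 1 surfaces alone.** Let f be the share of enrolled surfaces that are code 2. The documents do not give it, so 0 to 40% is an assumption. Take 6 as the number of enrolled surfaces per child, which is the unfavourable reading, since the protocol's 6 are sound. Then m = 6(1 − f), design effect = 1 + (m − 1) × 0.5, and effective surfaces per arm = 205 × m / design effect. Power is by the normal approximation for 25% vs 15%, which gives slightly higher values than Fisher's test.

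| f | m | Design effect | Effective n per arm | Power |
|---|---|---|---|---|
| 0 | 6.0 | 3.5 | 351.4 | 0.914 |
| 0.1 | 5.4 | 3.2 | 345.9 | 0.910 |
| 0.2 | 4.8 | 2.9 | 339.3 | 0.904 |
| 0.3 | 4.2 | 2.6 | 331.2 | 0.897 |
| 0.4 | 3.6 | 2.3 | 320.9 | 0.888 |

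**5. Power with both codes pooled.** Keep 25% vs 15% for sound surfaces and assume a 20% code 2 share with a 50% control rate. The control arm is 0.8 × 0.25 + 0.2 × 0.50 = 0.30.

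- No effect on code 2: 0.8 × 0.15 + 0.2 × 0.50 = 0.22. The difference is 8 points and power at n = 351 is 0.68.
- The same 40% relative reduction in code 2: 0.8 × 0.15 + 0.2 × 0.30 = 0.18. The difference is 12 points and power is 0.96.

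Over a wider set of assumptions (share 10 to 30%, code 2 control rate 40 to 60%, effect on code 2 from 0 to 20 points), pooled power at 205 children per arm runs from 0.51 to 0.99. The direction depends entirely on quantities that the documents do not state.

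**The case against.** The strongest reply is that *sound* is shorthand. Caries is diagnosed at the cavitation level, caries-free is glossed as no cavitation, and the allocation sentence says which surfaces are to receive an agent. On that reading one set is meant throughout. This is plausible, but the article gives sound surfaces a code of their own, so the text still conflicts and needs aligning.

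Second, including early lesions fits the rationale: the Discussion bases the SDF hypothesis partly on remineralisation of initial enamel lesions, and an enamel lesion kept from reaching cavitated dentine caries serves the stated objective. That stands for enamel lesions. It does not cover code 2 lesions already in dentin, nor a primary-prevention statement drawn from a pooled effect.

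Third, children are randomised individually, so code 2 surfaces are balanced in expectation and leaving the code out does not bias the arm comparison. That stands in full. The covariate list is also introduced in a way that need not be exhaustive, and an analysis plan that is not shown may add the code. That tempers the modelling point, but the list does name other baseline clinical covariates and passes over this one.

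A reader might also infer that code 2 surfaces are analysed but left untreated, and that the trial is therefore underpowered. The documents do not support this. It is a strained reading of the application steps, and the share, risk and effect in code 2 are all unstated.

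**Conclusion.** The inconsistency is real and rests on the text alone: enrolment and allocation admit codes 1 and 2, application and sample size refer to code 1, and the outcome denominator is silent. The baseline code is recorded, is not a named covariate, and is not captured by dmfs.

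The consequences are limited but worth removing. The arm comparison remains unbiased and the sample size stands for sound surfaces. What is lost is some precision and the ability to tell prevention on sound surfaces from slowed progression of lesions already present. Answering the primary-prevention question on code 1 alone costs little: power of about 0.91 falling to 0.89 for an assumed code 2 share of 0 to 40%, at 205 children per arm and with the protocol's rates and ICC. No specific power loss from pooling should be claimed.

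**What to change.** 1. Reconcile Eligibility Criteria, Recruitment and Examination, Interventions, Primary Outcome and Sample Size Calculation so that the enrolled, treated and analysed surfaces are the same set, stated in terms of the recorded codes. Which surfaces receive the agent is for the investigators to decide.
2. Include the baseline surface code (1 vs 2) as a surface-level covariate in the primary model, not subject to backward elimination.
3. Report the arm effect separately for code 1 and code 2, with an arm-by-code interaction, and rest any primary-prevention statement on code 1.

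The cost is some wording, one model term with its interaction, and one extra table. No new data are needed because the code is already collected. The code 1 estimate uses somewhat fewer surfaces, as shown above. The trial was not sized for the interaction, so the code-specific estimates should be read with their confidence intervals.
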